#### Cognitive function

The BSID III is a widely used measure of development in infants and toddlers. The BSID III consists of five scales of development: Cognitive, Language, Motor, Social-Emotional, and Adaptive Behavior scales; we are most interested in Cognitive scale results. The Cognitive scale contains 91 items that provide information about attention and anticipatory behavior, exploration of environment, object retention, cause and effect, object permanence, relational play, imitation, grouping, classification, memory, and problem solving. Administration time for children ≤ aged 12 months is less than 50 minutes. Raw scores from the Cognitive scale are converted to a scaled score, which can then additionally be converted to a composite score equivalent. Percentile ranks, confidence intervals (90 % and 95 % levels), growth score equivalents, and developmental age scores in months and days are available. The internal consistency for the Cognitive scale is 0.91. The BSID III is administered at 6 months corrected age by a trained, blinded examiner.

#### Prenatal risk factors

Maternal risk factors associated with neurodevelopmental outcomes include premature rupture of the membranes, pregnancy-induced hypertension, antenatal steroid or selective serotonin re-uptake inhibitor treatment, parity, chorioamnionitis, or diabetes mellitus [24, 25]. These data are included in the infant’s record and will be recorded after enrollment. Fetal or infant risk factors are intrauterine growth restriction, low 5-minute Apgar score, metabolic or respiratory acidosis within the first 24 hours of life, sepsis as defined by positive cultures, and evidence of intraventricular hemorrhage or periventricular leukomalacia on early and late cranial ultrasounds, which are routinely obtained in our setting at 2 weeks of life and at 34 to 36 weeks PMA [26, 27]. Data on these risk factors are available in the infant’s medical record and will be recorded by the study nurses. We will collect data for computing severity of illness using the Neonatal Medical Index (NMI), a tool we have used in previous studies [28]. The NMI summarizes infants’ medical condition with classifications ranging from 1 for infants born weighing ≥ 1000 g and without major complications to 5 for infants born weighing < 1000 g and with very serious complications. The scale distinguishes between the neurobehavioral performance of infants with varying degrees of illness and predicts developmental progress at 12, 24, and 36 months of age.

#### Immunologic measures

We collect blood within 7 days after birth in conjunction with a medically indicated blood draw for measurement proinflammatory cytokines. Nurses in the study setting draw the blood and place it in transport bags that have been left at the bedside. Study nurses check for samples each morning and transport samples to our laboratory. The laboratory uses a Bio-Plex (Bio-Rad, Hercules, CA, USA) multiplex suspension array system capable of measuring up to 100 different analytes simultaneously in small (12-μL) amounts of fluid in 1 well of a 96-well plate. Thus, only a small sample (0.5 mL) of blood is needed. Plasma and lymphocytes are separated using standard Ficoll gradient methods, and samples are divided into aliquots, frozen, and stored at −70 °C for batch assays. The assay accurately measures cytokine values in the range of 1–2500 pg/mL is precise (intra-assay coefficient of variability (CV) < 10 %, interassay CV < 15 %) and shows less than 1 % cross-reactivity among cytokines or with other molecules. Based on current literature and our own experienced, we use a customized panel to assay for cytokines of interest, including IL-1ra, IL-6, IL-8, IL-10, granulocyte-colony stimulating factor (GCSF), granulocyte macrophage colony stimulating factor (GMCSF), IFN-γ, monocyte chemotactic protein-1 (MCP-1), and TNF-α. All work with biohazardous materials is done in accordance with established laboratory safety guidelines.

#### Genetic measures

We collect saliva when infants are at the transition from gavage to oral feeding for genetic analysis using OrageneDNA® (DNA Genotek Inc., Kanata, Ontario, Canada), a collection kit that is non-invasive, intuitive to use, and stabilizes DNA at elevated temperatures, which facilitates transport and storage. Samples are frozen and stored for later analysis. We have selected a small number of theoretically and empirically determined genetic markers to assess including *ApoE* genotype (*ApoEε3*, *ApoEε2*, and *ApoEε4*) and the candidate genes mesenchymal epithelial transition factor (*MET*), neuregulin 3 (*NRG3*), and solute carrier family 6 member 4 (*SLC6A4*) [29]. We will use Applied Biosystems’ StepOnePlus® RT-PCR instrument and TaqMan® SNP genotyping assays (Life Technologies, ThermoFisher Scientific, Grand Island, NY, USA).

#### Neurobehavioral development

Both CNS development and autonomic nervous system (ANS) function are measured as indicators of neurobehavioral development. Sucking organization (suck bursts/feeding, burst duration, interburst interval) is a reliable measure of CNS function [30]. In addition, oral feeding performance (proportion consumed, efficiency) is a reliable indicator of CNS integrity [31]. These measures are taken during twice weekly observation feedings during Phase 2 of the intervention or, for infants in the usual care group, once oral feedings have started. To measure sucking, a noninvasive, piezoelectric sensor is placed on the infant’s jaw where it detects movements associated with sucking. A computer data acquisition system based on the Biopac Systems MP-150® data acquisition system is used to collect and store data (BIOPAC Systems, Inc, Goleta, CA, USA). Software developed by our team allows extraction and processing of the data from the acquisition file using algorithms developed by us.

Feeding performance consists of two measures: proportion consumed and efficiency. These measures have been reliably used in numerous feeding studies [32–34]. Proportion consumed, which incorporates both oral-motor skill and level of endurance, is the percent of prescribed formula or breast milk consumed over the feeding time, not counting breaks for burping or rest. The amount consumed is recorded at the end of the feeding. Efficiency refers to the total volume taken over feeding time and is a reflection of oral-motor skill as well as fatigue. The amount taken is recorded by the study nurse at the end of the observation feeding. Feeding time is calculated by the data acquisition system and eliminates non-feeding times (that is burping or rest breaks).

Heart rate variability (HRV) is a measure of ANS maturation and an indication of infant well-being and development [35, 36]. HRV increases with increasing PMA and, as the infant is more able to control breathing, an increase in parasympathetic activity occurs, as seen in the high frequency (HF) power spectrum of HRV. Both parasympathetic and sympathetic activity is seen in the low frequency (LF) power spectrum. Higher respiratory rates and activity result in a higher LF:HF ratio, consistent with a stress model. HRV effects have been found to be associated with poor autonomic organization during feedings. We examine HRV twice a week during observation feedings with data collected by the acquisition system described above. The electrocardiogram waveform is sampled at a rate of 1000 samples/second; the instantaneous R-R time interval is used for computation of HRV after being digitally filtered to remove artifact. HRV includes the LF and HF proportions (in normalized units) and the LF:HF ratio.

#### Clinical outcomes

Time to full oral feedings, the duration (in days) between the initiation of oral feeding and the achievement of full oral feeding, and length of stay, the number of days between the start of oral feeding and discharge to home, are also measured. Full oral feedings are achieved when the infant is consuming all nutrients orally by breast or bottle without intravenous supplementation or gavage feeding for 24 hours.

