**Methods:**

This trial uses an experimental, longitudinal, 2-group design with 120 preterm infants. Infants are enrolled within the first week of life and randomized to an experimental group receiving a patterned feeding experience from the first gavage feeding through discharge or to a control group receiving usual feeding care experience. The intervention involves a continuity of tactile experiences associated with feeding to train and build neuronal networks supportive of normal infant feeding experience. Primary outcomes are neurobehavioral organization as measured by Neurobehavioral Assessment of the Preterm Infant at 3 time points: the transition to oral feedings, NICU discharge, and 2 months corrected age. Secondary aims are cognitive function measured using the Bayley Scales of Infant and Toddler Development, Third Edition at 6 months corrected age, neurobehavioral development (sucking organization, feeding performance, and heart rate variability), and clinical outcomes (length of NICU stay and time to full oral feeding). The potential effects of demographic and biobehavioral factors (perinatal events and conditions of maternal or fetal/newborn origin and immunologic and genetic biomarkers) on the outcome variables will also be considered.

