Our intervention, a patterned feeding experience (PFE), is not currently used in most neonatal settings. The intervention is based on principles of neural plasticity and neuroprotection and is designed to take advantage of neuronal synaptic development and both experience-expectant and experience-dependent characteristics of the developing brain [13]. In addition, the intervention takes advantage of a regularly occurring caregiving and life-sustaining event in the life of an infant–feeding. The PFE intervention involves a continuity of tactile experiences associated with feeding to train and build neuronal networks supportive of the normal experience. There are virtually no accepted and no tested caregiver behaviors related to enteral feedings in preterm infants, although some recent research has produced evidence for a positive effect of greater caregiver sensitivity to the infant during feeding [14]. Theoretically, our intervention provided at a critical time in neurologic system development and associated with a recurring event such as feeding should enhance neural connections that may be important for later development, particularly language and other cognitive and neurobehavioral organization skills [15].

The overall objective of this study is to test the effect of a PFE from birth to NICU discharge for infants born at 32 weeks gestation and younger. The primary aim of the study is to test the effect of a PFE on neurobehavioral organization at 3 time points: the transition to oral feedings, NICU discharge, and 2 months corrected age (48 weeks PMA). Secondary aims are to test the effect of a PFE on 1) cognitive function at 6 months corrected age; 2) neurobehavioral development; and 3) clinical outcomes including time to first oral feeding, time to full oral feeding, and time to discharge. An exploratory aim is to describe the potential effects of perinatal and infant risk factors including immunologic and genetics influences on the outcome variables (neurobehavioral organization, cognitive function, neurobehavioral development, and clinical outcomes). We hypothesize that infants who receive the PFE will have improved neurobehavioral organization, cognitive function, neurobehavioral development, and clinical outcomes compared to infants who receive usual feeding care in the NICU.

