### Intervention

The study intervention has two phases using a tactile experience designed to pattern the neurologic system’s theoretical expectation for feeding experience. Phase 1, a period of “attended gavage,” begins within 24 hours of the first gavage feeding, which is generally provided before 72 hours of life. Attended gavage includes tactile containment during the entire gavage infusion by gravity plus 5 minutes. For infants too ill to be removed from the incubator, tactile containment consists of gentle hand containment (placing one hand lightly over the shoulder area and one hand lightly over the lower extremities). If medically stable, the infant is swaddled and removed from the incubator and held. Infants are also offered nonnutritive sucking (NNS) as part of every attended gavage feeding based on prior research showing that NNS facilitates behavioral organization. Instructions related to the tactile containment, swaddling/holding during gavage, and use of NNS are provided for all nursing staff and parents of infants in the intervention group. Gavage feedings are most often provided on a schedule of every 3 hours. Infants on continuous feedings, which may be needed for some infants primarily because of gastric reflux, receive the attended protocol every 3 hours for 15 minutes. Phase 1 of the intervention has varying duration, lasting as long as 12 weeks for infants born at 23 weeks PMA. Attended gavage is a change in practice for most NICUs so we use a team of well-trained study nurses who provide the attended gavage feedings for a minimum of 50 % of the feedings daily. Nursing staff or parents may provide additional attended gavage feedings. We record the occurrence of each attended feeding including who provided the intervention (parent, nursing staff member, or study nurse) and include that “dose” as a covariate in our analyses.

Phase 2 begins when infants in the intervention group begin oral feedings. When an oral feeding is attempted, the infant is held outside the incubator in a swaddled, flexed position either upright or side-lying. We record the volume of feeding prescribed and the amount consumed at each feeding. Infants who are unable to complete the prescribed volume orally or unable to orally feed receive attended gavage as described in Phase 1.

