The secondary aims require similar comparisons between study groups on secondary outcomes (cognitive functioning, neurobehavioral development, and clinical outcomes). To test secondary aim 1, differences between the 2 groups on the cognitive outcome measure (BSIDIII cognitive subtest scaled score) at 6 months corrected age will be tested using an ANCOVA with morbidity (NMI) and birth gestation used as covariates. To test secondary aim 2, 4 analyses will be performed, one for each of the feeding-related neurobehavioral outcomes (sucking organization, 2 measures of feeding performance, and HRV). The modeling will be done as above with a repeated-measures mixed-model approach with covariates (birth gestation, morbidity). To test secondary aim 3, separate ANCOVA analyses of the clinical outcomes (time to full oral feeding and length of stay) will be used to compare the 2 groups with the birth gestation age and morbidity covariates.

The intent of the exploratory aim is to identify risk factors of poor neurobehavioral development and cognitive dysfunction in preterm infants. We will test the assumed comparability of randomly assigned groups prior to undertaking further analyses. Secondary analyses will focus on the interactions between risk factors and the intervention differences by first screening the risk factors for effects at *P* = 0.2 and then developing a single exploratory model that includes all of the risk factors that significantly influence the outcome differences between the groups. Additional analyses will focus on the findings for neurobehavioral development including sucking organization and feeding performance, HRV, and clinical outcomes, first by examining the relationships between the risk factors and the components of neurobehavioral development and then by assessing the relationships among the components of neurobehavioral development and the primary outcome measure, the NAPI score (neurobehavioral outcome). The final goal is to identify a model of risk factors, modifiers (measures of neurobehavioral development), and mediators (intervention) that have an effect on the differences between groups.

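### Time to full oral feeding and length of stay are counted from the first oral feeding, a post-randomisation event the intervention is expected to bring forward, so any such shift is subtracted from the measured benefit

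*Protocol article*

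**What the plan says.** The Clinical outcomes section of the protocol article starts both clocks at the first oral feeding. Time to full oral feeding is "the duration (in days) between the initiation of oral feeding and the achievement of full oral feeding", and the other outcome is "length of stay, the number of days between the start of oral feeding and discharge to home".

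The timeline comes from two other places. The abstract states "Infants are enrolled within the first week of life and randomized to an experimental group". The Intervention section has attended gavage begin within a day of the first gavage feeding, and adds "Phase 1 of the intervention has varying duration, lasting as long as 12 weeks for infants born at 23 weeks PMA". It then says "Phase 2 begins when infants in the intervention group begin oral feedings". The first oral feeding is thus reached after randomisation and, in the PFE arm, after all of Phase 1.

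The outcomes are named differently in three places:

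- Abstract: "clinical outcomes (length of NICU stay and time to full oral feeding".
- Aims, in the Background: "clinical outcomes including time to first oral feeding, time to full oral feeding, and time to discharge", with the hypothesis that PFE improves clinical outcomes.
- Data management and analysis: "separate ANCOVA analyses of the clinical outcomes (time to full oral feeding and length of stay", adjusted for birth gestation and morbidity (the Neonatal Medical Index, NMI).

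Time to first oral feeding appears in the aims, but it is not defined under Clinical outcomes and is not among the outcomes tested for secondary aim 3.

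**The concern.** Randomisation makes the arms comparable at enrolment. It does not make them comparable at a later event whose timing may depend on the arm. Here that event is both an outcome PFE is expected to improve and the starting point for the two outcomes that are tested. An earlier start, which the trial would count as success, lengthens both intervals unless the end date moves by at least as much.

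The planned covariates do not repair this. Birth gestation and the NMI adjust for how mature and how ill the infant is. They do not adjust for a start date that treatment has moved. Because time to first oral feeding is not in the list of tested outcomes, no analysis in the article would show an offsetting shift.

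At stake is the interpretation of both tests under secondary aim 3, and a result reported as length of stay that covers only the last part of the stay.

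**Working it through.** **Inputs from the protocol article.** There are 120 infants, 60 per group, with 20% attrition (Sample; Power analysis). That leaves 120 × 0.80 = 96, or 48 per group. Tests are two-sided at 0.05. The article gives no SD for the clinical outcomes and no expected shift in first feeding, so the shifts and SDs below are assumptions.

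**The plan's own figure.** Power for secondary aim 3 is taken by analogy from secondary aim 1: difference 2, SD 3, power 89%. With 48 per group the exact t calculation gives 89.8% and the normal approximation 90.4%, so the figure reproduces. The point here concerns the outcome definition and does not depend on it.

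**Identity.** Let k be the days by which PFE advances the first oral feeding, and m the days by which it advances the endpoint (full feeding or discharge).

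- Difference as defined (PFE minus control) = (−m) − (−k) = k − m.
- Difference counted from birth = −m. From randomisation it is the same in expectation, because age at randomisation is balanced by design.

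A negative value favours PFE.

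| k (assumed) | m (assumed) | As defined, k − m | From birth, −m | Reading |
|---|---|---|---|---|
| 0 | 5 | −5 | −5 | no bias |
| 3 | 7 | −4 | −7 | benefit understated |
| 7 | 7 | 0 | −7 | benefit hidden |
| 7 | 5 | +2 | −5 | sign reversed |
| 7 | 3 | +4 | −3 | sign reversed |

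**Chance of a significant result in the wrong direction.** With 48 per group, SE = SD × √(2/48) = 0.204 × SD, and P(significantly worse for PFE) = 1 − Φ(1.96 − (k − m)/SE), ignoring covariate adjustment.

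| SD in days (assumed) | SE | k = 7, m = 3 | k = 7, m = 5 |
|---|---|---|---|
| 7 | 1.43 | 0.80 | 0.29 |
| 10 | 2.04 | 0.50 | 0.16 |
| 14 | 2.86 | 0.29 | 0.10 |

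With k = 3 and m = 7 the test still points the right way. It is significant for PFE with probability 0.80, 0.50 and 0.29 at the same three SDs, but for a difference of 4 days rather than 7.

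**Labels side by side.** The abstract's NICU stay includes the gavage period, and the Clinical outcomes definition leaves it out. For an infant with the longest Phase 1 that the article mentions, about 12 × 7 = 84 days of stay fall outside the outcome called length of stay.

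**The case against.** The best case for the plan is that the interval from first to full oral feeding is a clearly defined and clinically meaningful measure of how fast the transition goes. It removes much of the variation due to birth gestation, and the outcomes are secondary. Most of this stands. The trial is powered for the primary aim, the primary analysis of neurobehavioral organization is not affected, and the interval is worth reporting.

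Several stronger readings are tempting, but the article does not support them:

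- *Reversal is to be expected.* It occurs only if first feeding advances by more days than the endpoint. The article gives no timing or expected shift for first feeding, so how likely this is cannot be judged from it.
- *All benefit gained during attended gavage is lost.* If Phase 1 makes the transition faster once oral feeding has begun, the interval captures that. Only the part that acts by moving the start date is lost.
- *The definition contradicts the aim's time to discharge.* The aims give no origin for that time, so the later section supplies one. The clear mismatch is with the abstract.
- *Infants removed at 40 weeks PMA have the longest times.* They are removed because they cannot move to oral feeding, so on the plan's clock they have no start date and the outcome is undefined for them. How infants without the event are handled may be set out in the full protocol or analysis plan. The article does commit to an intent-to-treat analysis.
- *ANCOVA is the fault and a Cox model is required.* The time origin is the problem, and it would persist under any model.

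**Conclusion.** The point holds in conditional form. Both tested clinical outcomes start at a post-randomisation event that the trial expects PFE to bring forward. The measured difference equals the endpoint shift minus the first-feeding shift, and the planned covariates cannot correct that. The benefit is understated when first feeding moves earlier, reads as zero when the shifts are equal, and changes sign when first feeding moves further than the endpoint. If first feeding does not move, there is no bias.

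The identity is exact and needs no assumption. The sizes shown (4 days worse as defined against 3 days better from birth, with a wrong-direction significant result in 29% to 80% of trials for SDs of 14 to 7 days) rest on assumed shifts and SDs and are illustrations only.

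Two inconsistencies add to it: length of stay as defined is not the NICU stay named in the abstract, and time to first oral feeding is an aim without a listed test. This should be fixed. It is limited to secondary aim 3.

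**What to change.** In Clinical outcomes and in Data management and analysis:

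1. Define time to first oral feeding, time to full oral feeding and length of NICU stay, all counted from birth or from randomisation, and list all three for analysis.
2. Compare the arms with the planned birth gestation and morbidity (NMI) covariates. A Cox model is not required.
3. Report the interval from first to full oral feeding as a supportive transition measure, under a name that cannot be taken for length of stay.
4. Include infants who do not reach the event by a method that does not assume non-informative censoring. For example, treat death or removal for inability to feed orally as a competing event or as the worst rank. Simply censoring infants removed because they cannot feed orally would not be appropriate.
5. Use the same outcome names in the abstract, aims, definitions and analysis.

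Cost: mainly redefinition, since the clinical outcomes come from the health record. Two limits apply. The article does not show that later dates are collected for infants taken out of the study at 40 weeks PMA, so item 4 applies as far as those dates are available. Times from birth also vary more with birth gestation; the planned covariate reduces this variation but may not remove all of it, so some precision may be lost.
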